To address this unmet need, we have designed the Shenzhen Neonatal Stroke Online Registry. In this study, we hypothesize that implementing a standardized, multicenter, prospective cohort will yield accurate epidemiological data, identify key risk factors associated with adverse outcomes, and establish a robust platform for developing prognostic models. We present the protocol for a six-year, prospective, observational cohort study involving 22 hospitals in Shenzhen. The primary objectives are to determine the registry-based incidence of neonatal stroke and to evaluate comprehensive neurodevelopmental outcomes at 5 years of age. Secondary objectives include characterizing stroke subtypes, analyzing current management disparities, and integrating a biobank for future mechanistic research. This protocol aims to provide a replicable model for disease surveillance and to generate high-quality evidence to inform clinical guidelines, optimize care pathways, and ultimately improve long-term outcomes for infants affected by stroke.

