#### Secondary objectives

2.1.2

To characterize the clinical presentation, short-term treatment efficacy, and safety of the three subtypes of neonatal stroke: arterial ischemic stroke, cerebral sinovenous thrombosis, and hemorrhagic stroke.To identify significant prenatal, perinatal, and postnatal risk factors for neonatal stroke, and to develop and validate predictive models for risk stratification using a panel of early biochemical and imaging biomarkers.To analyze regional and institutional variations in the diagnostic, therapeutic, and rehabilitative management of neonatal stroke, and to propose evidence-based strategies for optimizing care and standardizing treatment protocols.

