### Sample size calculation

2.6

Assuming a 30% neurodevelopmental outcome rate at 5 years (based on published literature), a final sample of approximately 210 evaluable participants would yield 60–80 outcome events. With a maximum of 6–8 candidate predictors, this yields an events-per-variable ratio of approximately 10, exceeding the recommended minimum for logistic regression to avoid overfitting. Internal validation will be performed using bootstrap resampling (1,000 repetitions) to estimate optimism-corrected performance. Total enrollment of 300 accounts, with 10% mortality and 20% loss to follow-up, and the understanding that the final evaluable sample will be approximately 210 participants.

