### Statistical analysis plan

2.7

All analyses will be performed using SPSS (Version 27.0) and R (Version 4.4.1).
Descriptive Statistics: Continuous data will be presented as means ± SD (for normally distributed data) or as medians [IQR] (for non-normally distributed data). Categorical data will be analyzed using Chi-square or Fisher's exact tests.Incidence and Survival Analysis: Registry-based incidence and survival rates will be stratified by gestational age, sex, birth weight, and hospital level.Predictive Model Development:
Predictor Selection: LASSO regression will be used to identify potential predictors.Model Building: Multivariable logistic regression will identify independent factors associated with poor neurodevelopmental outcomes.Model Validation: Internal validation using bootstrap resampling (1,000 repetitions) will assess model performance (discrimination, calibration, and clinical utility).A two-sided *p*-value < 0.05 will be considered statistically significant.

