One of the major contributions of this study is its focus on long-term neurodevelopmental outcomes, addressing a significant knowledge gap in China. International research has shown that between 20% and 50% of pediatric stroke survivors develop long-term cognitive impairments, including language deficits, memory decline, intellectual disabilities, and attention deficits, with some chronic language impairments persisting into adolescence (18, 19). However, these data largely derive from pediatric stroke cohorts that include children beyond the neonatal period. The developmental trajectory and neuroplasticity profile of neonatal stroke differ substantially from later childhood stroke due to the unique vulnerability of the developing brain (e.g., impaired myelination, synaptic pruning abnormalities) and its greater potential for reorganization. Where possible, we will present neonatal-specific outcomes separately. This study represents the first prospective registry-based cohort of neonates with stroke in China, incorporating a biobank of biological samples, including stool and breast milk, and tracking patient outcomes up to 5 years of age. The comprehensive nature of this cohort, which includes detailed neurodevelopmental assessments, will significantly advance standardized management of neonatal stroke nationwide.

We acknowledge that neonatal stroke comprises biologically and prognostically heterogeneous subtypes (arterial ischemic, hemorrhagic, venous sinus thrombosis). Subtype-specific analyses are planned for all primary and secondary outcomes.

The prospective design of this study offers substantial clinical and societal benefits. It is expected to deepen the understanding of neonatal stroke, enhance the management of pregnant women with underlying risk factors, and provide tailored guidance for delivery planning. Furthermore, the protocol mandates early cranial MRI and video EEG testing for infants presenting with postnatal seizures, ensuring prompt and accurate diagnosis. These measures are crucial for the early identification and management of neonatal stroke, facilitating timely interventions and better prognostic outcomes.

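### Section 2.7 reads independent factors off an ordinary logistic refit after LASSO on the same data, so p-values and intervals of retained variables are not valid at their nominal level (minor)

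*Protocol article*

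**What the plan says.** Section 2.7 (Statistical analysis plan) sets out the prognostic model in sequence. First, "LASSO regression will be used to identify potential predictors". Then, "Multivariable logistic regression will identify independent factors associated with poor neurodevelopmental outcomes". Bootstrap resampling with 1,000 repetitions follows, to judge discrimination, calibration and clinical utility. The section closes with one general rule, that a two-sided p "value < 0.05 will be considered statistically significant", and attaches it to no particular step.

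Section 2.6 gives the dimensions. "Assuming a 30% neurodevelopmental outcome rate at 5 years", about 210 evaluable children are expected to supply 60–80 events, "With a maximum of 6–8 candidate predictors".

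The Introduction hypothesises that the cohort will "identify key risk factors associated with adverse outcomes". The Discussion adds: "Subtype-specific analyses are planned for all primary and secondary outcomes". Incidence is the only primary outcome (section 2.5.1); risk-factor characterisation and model performance are secondary (section 2.5.2). The word exploratory is used for biobank work (section 2.4.5) but not for the factor analyses.

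**The concern.** LASSO keeps a variable because it is associated with the outcome in these data. Testing the survivors again in the same data, as if they had been named in advance, uses that association twice. A variable with no real effect is retained mainly when chance has already given it an apparent one, so its refit p-value is too small and its interval sits too far from an odds ratio of 1.

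This concerns a method the text states, not one it leaves out: the order of the steps and the claim drawn from the second step are both in section 2.7. At stake is how a reader takes the word independent. The Introduction hopes the results will feed into guidelines and care pathways. A retained variable printed with p<0.05 would be read as a 5% test that has been passed, which it is not.

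**Working it through.** **Inputs.** From section 2.6: 300 enrolled, 10% mortality, 20% loss to follow-up, 30% outcome rate, 6–8 candidates. From section 2.7: LASSO, then logistic regression, two-sided 0.05. Assumptions, because the article does not give them: normally distributed candidates, correlation 0 or 0.5, LASSO penalty chosen at minimum cross-validated deviance and, where true effects are present, log-odds of 0.8 and 0.6 per SD.

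**1. The plan's own figures.** 300 × (1 − 0.10 − 0.20) = 210 evaluable. 210 × 0.30 = 63 events, inside the stated 60–80. Both reproduce.

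**2. Reference: all candidates in one model, no selection.** If no candidate matters, the chance of at least one p<0.05 should be 1 − 0.95^6 = 0.265 or 1 − 0.95^8 = 0.337. Simulation (n=210, 30% events, 3,000 runs) gave 0.271 and 0.346. Per predictor, that is 1 − (1 − 0.271)^(1/6) = 0.051 and 1 − (1 − 0.346)^(1/8) = 0.052. The full model holds its 5% level.

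**3. The plan's sequence: LASSO, then ordinary refit on the same data (n=210, 30% events).**

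| Setting | True predictors | Retained nulls with p<0.05 | At least one false p<0.05 per study |
|---|---|---|---|
| 6 or 8 candidates, correlation 0 or 0.5, 10-fold, 600 runs each | none | 34–35% | 20–25% |
| 8 candidates, correlation 0, 5-fold, 400 runs | none | 32% | 24% |
| 8 candidates, separate run | none | about 37% | not available |
| 2 true + 6 null, correlation 0, 10-fold, 600 runs | two | 14.9% | 29% |
| 2 true + 6 null, correlation 0.5, 10-fold, 600 runs | two | 13.4% | 25.5% |
| 8 candidates, separate run | two | about 12% | not available |

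The nominal value for the third column is 5%.

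**4. Where the distortion sits.** In the 5-fold run LASSO kept 0.9175 null variables per study on average, and 31.9% of them reached p<0.05. That is 0.9175 × 0.3188 = 0.29 false results per study, or 0.29 / 8 = 3.7% per candidate. Counted over all candidates, the rate is not inflated. Counted over the variables that are reported, it is about six times nominal (0.319 / 0.05 = 6.4). LASSO removes nulls that look unremarkable and passes on those that look striking.

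**5. Intervals.** A Wald 95% interval excludes an odds ratio of 1 exactly when the Wald p-value is below 0.05. For retained nulls, coverage is therefore 1 − 0.37 to 1 − 0.32, or 63–68%, with no true predictor, and 1 − 0.15 to 1 − 0.12, or 85–88%, with two.

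**6. Does the bootstrap repair it?** Sections 2.6 and 2.7 give it one job, optimism-corrected model performance. Nothing in the text applies it to the coefficients' p-values or intervals.

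**7. Sensitivity.** Section 2.6 calls the 6–8 variables candidates, so they are taken here as the set LASSO starts from. If LASSO instead started from 30 (an assumption), 49% of retained nulls reached p<0.05.

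**The case against.** The best defence is that section 2.7 never says p<0.05 decides independence. LASSO selects, logistic regression builds, the bootstrap validates, and the p-value sentence is a general closing line. That is right as a reading of the words, and it is why the point is conditional. But no other significance criterion is offered, and naming independent factors from a multivariable logistic model is usually done by its p-values.

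Second, the no-effect setting is extreme. The Introduction itself cites imaging findings that correlate with motor outcome, so some candidates are likely to be real. This stands, and it makes the lower range, about 12–15%, the more relevant one. That is still two to three times nominal.

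Third, LASSO slightly lowers the whole-study error when nothing is real: 24%, against 34.6% in the full model with 8 candidates. This also stands. The fault lies in the inference on retained variables, not in a larger number of false claims.

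A reader might go further and infer that false-positive claims are likely, that the plan has no hierarchy, or that three subtype analyses push the chance of a false finding to 62–75%. The article does not support these readings:
- In the pooled cohort the chance is roughly 20–35%.
- Primary and secondary outcomes are separated. Finer ordering or alpha allocation is detail that a condensed article may leave to a full plan, and no confirmatory test is specified here.
- The 62–75% figures need all 8 predictors significance-tested in three equal subtypes. Section 2.7 describes no such tests, and the single Discussion sentence would be met by stratified estimates.

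Nor do these figures carry over to the section 2.1.2 aim "To identify significant prenatal, perinatal, and postnatal risk factors for neonatal stroke". That concerns risk of stroke, whereas the 6–8 candidates and the LASSO step concern prognosis among cases.

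**Conclusion.** The point holds in narrow form and is minor. If independence is judged by the refit p-values, which is the usual reading but not an explicit one, then about 12–15% of retained null predictors (two true predictors of assumed strength) to 32–37% (none) would pass a nominal 5% test, and the matching 95% intervals under-cover. The result rests on 210 children, about 30% events and 6–8 candidates from section 2.6, and on the assumed effects, correlations and penalty rule listed above. It does not touch the incidence estimate or the planned assessment of predictive performance.

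**What to change.** In section 2.7:

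1. Describe variables kept by LASSO as predictors in the model, not as independent factors, and report how often each is selected across the 1,000 bootstrap resamples already planned. LASSO must be rerun within each resample to obtain this.
2. Take any association estimates, 95% confidence intervals and p-values from the single logistic model containing all 6–8 pre-listed candidates, not from the refit after LASSO.
3. Label these factor analyses, and any subtype analyses, exploratory.

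False-discovery control is optional. The exploratory label matters, because the full model gives valid p-values for each predictor but does not lower the chance that one of several crosses 0.05 (step 2 of the working).

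The cost is wording and trivial extra analysis, with no additional patients or data. Intervals will be slightly wider: with 63 events the full model has 63 / 6 = 10.5 events per variable for 6 candidates and 63 / 8 = 7.9 for 8. Fewer factors can be presented as independent or significant.

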### Safety assessment

2.8

Data Security: All data will be de-identified and stored securely on password-protected servers.Adverse Event Monitoring: Adverse events related to clinical care or follow-up will be documented in accordance with institutional protocols.Oversight: The Clinical Research Data Monitoring Committee will conduct biannual reviews of study progress and data quality.

## Discussion

3

This study addresses a critical gap in neonatology and pediatric neurology in China by establishing the Shenzhen Neonatal Stroke Online Registry Database and implementing the nation's first large-scale multicenter, prospective cohort study of neonatal stroke. Consistent with international efforts, such as the Italian Registry of Infantile Thrombosis (RITI), our registry aims to provide continuous, standardized monitoring of aetiology and prognosis (9). While several other countries (6, 7) have successfully established online registries to continuously monitor etiology and prognosis, China currently lacks a dedicated national registry and has not conducted a prospective multicenter study in this field. The establishment of this registry is paramount as it will facilitate the collection of large-volume data, enable sophisticated analysis for quality improvement, support the construction of robust prognostic models, and ultimately promote earlier diagnosis and improved outcomes for neonatal stroke, especially given that neonatal stroke has not yet been incorporated into projections showing the rising incidence and prevalence of adult stroke over the next three decades (16, 17).

The collaboration among the twenty-two participating institutions is a cornerstone of this study, enabling seamless data sharing and ensuring comprehensive, full-cycle neurodevelopmental management from the perinatal period through preschool age. This collective effort will enable continuous monitoring of patient outcomes, ensuring that the diagnosis, treatment, and rehabilitation of neonatal stroke are consistent and well coordinated across institutions.

One of the major contributions of this study is its focus on long-term neurodevelopmental outcomes, addressing a significant knowledge gap in China. International research has shown that between 20% and 50% of pediatric stroke survivors develop long-term cognitive impairments, including language deficits, memory decline, intellectual disabilities, and attention deficits, with some chronic language impairments persisting into adolescence (18, 19). However, these data largely derive from pediatric stroke cohorts that include children beyond the neonatal period. The developmental trajectory and neuroplasticity profile of neonatal stroke differ substantially from later childhood stroke due to the unique vulnerability of the developing brain (e.g., impaired myelination, synaptic pruning abnormalities) and its greater potential for reorganization. Where possible, we will present neonatal-specific outcomes separately. This study represents the first prospective registry-based cohort of neonates with stroke in China, incorporating a biobank of biological samples, including stool and breast milk, and tracking patient outcomes up to 5 years of age. The comprehensive nature of this cohort, which includes detailed neurodevelopmental assessments, will significantly advance standardized management of neonatal stroke nationwide.

We acknowledge that neonatal stroke comprises biologically and prognostically heterogeneous subtypes (arterial ischemic, hemorrhagic, venous sinus thrombosis). Subtype-specific analyses are planned for all primary and secondary outcomes.

The prospective design of this study offers substantial clinical and societal benefits. It is expected to deepen the understanding of neonatal stroke, enhance the management of pregnant women with underlying risk factors, and provide tailored guidance for delivery planning. Furthermore, the protocol mandates early cranial MRI and video EEG testing for infants presenting with postnatal seizures, ensuring prompt and accurate diagnosis. These measures are crucial for the early identification and management of neonatal stroke, facilitating timely interventions and better prognostic outcomes.

Additionally, this study underscores the importance of multidisciplinary collaboration and the critical role of follow-up care in early rehabilitation. By emphasizing early diagnosis, intervention, and long-term follow-up, this research will contribute to a more refined and integrated management system for both perinatal medicine and pediatric care. The anticipated outcomes of this study not only hold promise for reducing the financial and emotional burdens faced by families but also offer significant improvements to national health standards, particularly by enhancing the quality of care for neonatal stroke across China.

However, it is important to acknowledge several limitations of this study. As an observational design, it cannot control for all potential confounding variables, limiting its ability to establish causality. The five-year follow-up period is prone to attrition bias, especially if dropouts are associated with disease severity or socioeconomic factors. Despite standardized protocols, the manual data entry across multiple institutions is vulnerable to inconsistencies and inter-rater variability. Furthermore, the findings may have limited generalizability outside of Shenzhen due to regional differences in demographics, healthcare access, and clinical practices. Moreover, during the 5-year enrollment and follow-up period, MRI protocols, neonatal care standards, and antiepileptic treatment strategies may evolve, potentially influencing outcomes. We will document any major practice changes and adjust analyses accordingly. These limitations should be considered when interpreting the study results and formulating future research directions.
